### Data Collection Methods

Collection of data on outcomes, baseline characteristics, birth plan, and other trial data will be collected automatically by the app. All study questionnaires were developed specifically for this study, and screenshots are available in Multimedia Appendices 1-8.

### Pilot Intervention and Adjustments

A pilot intervention was conducted with 1000 participants prior to the final study for final adjustment of the questionnaires’ linguistic adequacy and to evaluate the optimal sequence of missions to be administered to the participants. Engagement in the study questionnaires was higher than expected.

### Data Management

For this study, a series of data management procedures will be implemented to ensure data protection, safety, privacy, and confidentiality. Data management will target the following three aspects: participant data treatment by the app’s parent company, relevant information transfer to researchers, and data set maintenance by all teams. It is worth mentioning that in compliance with security measures established by the general data protection law [50,51] and the resolutions of the National Council of Health for human experimentation [52], researchers will receive only the variables of interest for the study.

At the individual level, the collected data will be computed directly in the parent company’s system. This will include the following: verification of the individual's registration, deidentification of the data and separation of the population data for this study from the rest of the platform data, and the creation of an individual cloud to store the data for this specific study. Only the variables of interest in the deidentified data of the study participants will be used.

When accepting the app’s terms of use and privacy policy, all users have their data automatically pseudo-anonymized (ie, unidentifiable). These data include the following: personal data collected upon registration; complementary data captured during app use, such as a version of the smartphone’s operating system or device model; and all user responses during interventions.

At the level of database management by the researchers, the file will be initially processed within the app’s servers, where the raw data files will also be stored and will not be used for any purpose other than this study.

### Data Analysis Plan

#### Statistical Analysis

CONSORT (consolidated standards of reporting trials) guidelines will be used in reporting the results. An intention-to-treat analysis will be performed to compare data from the study's entry and exit surveys. This approach promotes a pragmatic assessment of the potential benefits of the intervention, as it incorporates loss to follow-up in the analyzed data of the intervention group.

Sociodemographic characteristics will be analyzed using descriptive statistics; between-group comparisons will be performed using chi-square analysis or a 2-tailed *t* test. For all group comparisons, the results shall be expressed as an effect (or relative risk for binary outcomes), corresponding 2-sided 99% confidence intervals (α=1%; power=80%), and associated *P* values. Adjusted analyses using baseline variables shall be performed using regression analysis to determine the continuing influence of key baseline characteristics on the outcomes, including female app users in the public and private sectors, cesarean sections, and vaginal delivery. The analyses will be conducted using the R statistical analysis software (The R Foundation) [53].

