### Study Setting

The study will be conducted through the restricted segment of a smartphone app. This app has been especially designed for behavior and opinion research in Brazil and will be used for participant recruitment, assessment of eligibility criteria, delivery and control of the intervention, and data collection.

Currently, the app has registered approximately 1,360,000 active users. Of them, 98,518 have accessed the internet in the past 14 days (September 2020); these individuals will be primarily invited to participate at the recruitment stage, reaching women with different socioeconomic and demographic characteristics in all States of Brazil.

All communication with participants will be carried out within the native and private environment of the app. Engagement will be voluntary, and participants will be financially reimbursed for the value of mobile internet use. The estimated compensation for participation in this study was set between R $5.00 and R $10.00 (US $0.92-$1.84), depending on the extent of participation, to cover the cost of mobile internet usage.

The stages of the study conducted through the app will be comprised of interactive questionnaires (called “missions” in the app), which are opportunities for engagement through direct communication with users. The questionnaires are as follows:

Eligibility criteria filter: the filter has 7 questions related to the study variables (intention to have biological children, number of children, those born through normal delivery, year of birth of the oldest child, race, education, and occupation) (Multimedia Appendix 1)Invitation to participate in the study: information on the study and the investigators, objective of the study, and the dynamics of the missions (Multimedia Appendix 2)Questionnaire to complete and validate the informed consent form: split across different screens, digitally validated by the participant (Multimedia Appendix 3)Entry questionnaire: prospecting of values and preferences associated with the intended care (Multimedia Appendix 4)Questionnaires on childbirth (intervention group) (Multimedia Appendix 5) or on diaper use (control group) (Multimedia Appendix 6)Exit questionnaire: similar to the entry questionnaire (Multimedia Appendix 4)Birth plan questionnaire (Multimedia Appendix 7)

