### Allocation and Randomization

Users will be recruited through the app, which is voluntarily installed by the user. Registrations are carried out organically, with no active screening for users and no advertising. Once registered, the new user answers questions related to his/her socioeconomic data. Missions will be sent to the profiles of users of all social classes (paired to represent the composition of the Brazilian population in the 5 regions of the country) and aged between 18 and 49 years.

Randomness in the sample is guaranteed in the program architecture of the missions, ensuring that those who undertake 1 mission will not be able to access the other mission, by blocking the mission ID through the execution of filters. On the app screen, the respondent sees only the name of the mission, with no indication of whether that participant is in the intervention or the control arm. To guarantee greater confidentiality and not induce interests or scams, we assigned the same name to the 2 missions: “Being a mother is making choices.” To balance the sample, the statistician team distributes the sample on the basis of the “n” defined for the study, thus generating a balance between the geographical region and economic class.

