### Outcomes

#### Primary Outcomes

The primary outcome measures (Table 1) will be the following:

Preference reported for the gestational outcome (for a healthy woman and neonate) the safety of which is determined on the basis of evidence: waiting for spontaneous onset of labor; waiting for the full 39 weeks; preference for vaginal childbirth; preference for cesarean delivery after labor; preference for elective cesarean delivery; or indifference.Differences between the responses in the elaboration of the birth plan, aligned with the information provided in the intervention, in accordance with the Ministry of Health guidelines.Knowledge of the COVID-19 pandemic’s impact in childbirth care and alternatives available.

**Table 1 table1:** Outcomes of interest and definitions.

Endpoints	Definitions
Engagement in the intervention	Proportion of invited women who finish the missions
Reduced interest in elective cesarean section	Reduction in the proportion of women who intend to schedule an elective cesarean section
Increased engagement in seeking protagonism or informed choice	Proportion of women who develop a birth plan
Knowledge of the safest, most effective options associated with a more positive experience	Safer, more effective choices associated with a more positive experience in the exit survey and the birth plan
Engagement or desire to elaborate and share the experience and concerns	Elaboration of a narrative of the experience, doubts, and expectations regarding childbirth
Knowledge of the options available during the COVID-19 pandemic	Responses compatible with the information offered

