### Parameters for Calculating the Sample Size

The sample size was calculated in accordance with the following parameters:

Study population size: in total, 32,000 women of reproductive age registered through the app (data collected from July 2019 before the onset of the COVID-19 pandemic).Prevalence of the outcome of interest: a prevalence of 2.6% (Murcia, Spain) and 3% (São Paulo, Brazil) in the delivery rate of the birth plan to the obstetric care service.Estimated impact of the intervention: a previous study that aimed to verify the effectiveness of a crowdsourcing strategy in promoting testing for hepatitis among men who have sex with men in China achieved a rate of 72.1% for the visualization of the multimedia components of the intervention. An increase in the number of tests performed was reported among 17.4% of the participants and confirmed by sending pictorial evidence of the examination among 7.9% of the participants [48]. In this study, a 20% impact on the outcome of preference for the elective cesarean section was estimated.Margin of error and safety: considering that part of the parameters used during sampling was estimated from other studies and the possibility of loss to follow-up among a portion of the recruited women, a type I error (α) margin of 1% was adopted with a 99% confidence level, along with a safety margin for type II error (β) of 20%.

Thus, at least 9068 participants in each group will be required to demonstrate the effect of the educational intervention on the outcome measures of interest [49]. We expect to have 10,000 participants in each group. Expected recruiting numbers (approximate, depending on engagement) are detailed in Multimedia Appendix 9.

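### The planned regression is aimed at what predicts the outcome rather than at an adjusted treatment effect, and the entry-exit wording leaves the primary contrast open

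*Protocol article*

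**What the plan says.** Under Statistical Analysis, the only tests named for comparing groups are the chi-square test and the two-tailed t test. Results for all group comparisons are to be given as an effect, or a relative risk for binary outcomes, with 99% intervals. Regression then appears with its own purpose: "Adjusted analyses using baseline variables shall be performed using regression analysis to determine the continuing influence of key baseline characteristics on the outcomes". The list that follows is introduced as examples and names public or private sector, cesarean sections and vaginal delivery.

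The same section describes the intention-to-treat analysis as setting the entry survey against the exit survey. Table 1 defines one endpoint as "Reduction in the proportion of women who intend to schedule an elective cesarean section", without saying whether the reference is the entry survey or the control arm. The Methods paragraph of the Abstract, by contrast, says that the groups will be compared in their birth-plan, entry and exit responses.

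Two other places show what is available for adjustment. Study Setting lists "Exit questionnaire: similar to the entry questionnaire", and the Abstract places the entry questionnaire before allocation. Allocation and Randomization says that the statistical team distributes the sample, "generating a balance between the geographical region and economic class".

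**The concern.** Two things are left unsettled.

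The first is the role of adjustment. A regression that asks which baseline characteristics influence the outcome answers a different question from one that estimates the effect of the intervention given baseline. For an attitude item asked before and after, the entry answer is likely to be among the strongest predictors of the exit answer. If it is not used in the effect estimate, precision that costs nothing is lost, and any chance imbalance at entry stays in the estimate.

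The second is the contrast itself. A fall from entry to exit within the intervention arm also contains the effect of being asked similar questions twice within about 12 days (Participant Timeline). Only the contrast between arms is protected by randomisation. A reader of the intention-to-treat sentence and Table 1 cannot tell which of the two will be reported as the effect on elective cesarean preference.

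**Working it through.** **The plan's own figure.** Parameters for Calculating the Sample Size asks for 9068 per group. The inputs are "a prevalence of 2.6% (Murcia, Spain) and 3% (São Paulo, Brazil) in the delivery rate of the birth plan", a 20% impact (read here as relative), "a type I error (α) margin of 1% was adopted with a 99% confidence level" and a type II error of 20%. The Statistical Analysis section makes the intervals two-sided. With the pooled two-proportion formula, n = [z₁√(2p̄(1−p̄)) + z₂√(p₁(1−p₁)+p₂(1−p₂))]² / (p₁−p₂)², z₁ = 2.576 and z₂ = 0.842:

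- 3% to 2.4%: 17,045 per arm
- 2.6% to 2.08%: 19,740 per arm
- 3% to 3.6%: 20,704 per arm
- 2.6% to 3.12%: 23,998 per arm

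So 9068 is not reproduced from the stated inputs. Some unstated variants come close (for example one-sided 5% at 3% versus 2.4% gives 9023), but none can be confirmed. This is a separate matter, and the present point does not rest on it. The figure 9068 serves below only as a reference size.

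**Precision.** The article gives no entry-exit correlation r, so r is an assumption, varied from 0.2 to 0.7. With equal variances at entry and exit, and relative to an exit-only comparison:

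- adjustment for the entry answer multiplies the variance by 1 − r²;
- a change score multiplies it by 2(1 − r);
- the interval width under adjustment is multiplied by √(1 − r²).

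| r (assumed) | 1 − r² | Width | Size matching 9068 unadjusted | 2(1 − r) |
|---|---|---|---|---|
| 0.2 | 0.96 | 0.98 | 8706 | 1.6 |
| 0.3 | 0.91 | 0.95 | 8252 | 1.4 |
| 0.5 | 0.75 | 0.87 | 6801 | 1.0 |
| 0.7 | 0.51 | 0.71 | 4625 | 0.6 |

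The fourth column is 9068 × (1 − r²), rounded up.

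Since 2(1 − r) − (1 − r²) = (1 − r)² ≥ 0, a change score is never more precise than adjustment. It is worse than exit data alone when 2(1 − r) > 1, that is, when r < 0.5.

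**Illustration in power.** Take 3% versus 2.4%, two-sided alpha 1% and 10,000 per arm, with effective size 10,000/(1 − r²). Power is 52% unadjusted, and 54%, 57%, 67% and 86% at r = 0.2, 0.3, 0.5 and 0.7. This is only an illustration, because the 3% is a birth-plan delivery rate while the 20% refers to elective cesarean preference.

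**Scope.** These factors apply to items asked at both entry and exit. No entry counterpart is described for birth-plan responses, for completing the missions or for developing a birth plan. For these, only region, class and related entry answers can be used.

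**The case against.** The strongest case against the point is that adjusted analyses are planned, in the very sentence quoted, and that the variable list is open-ended. The exact covariates may stand in an analysis plan that is not shown. The clause naming the chi-square and t tests follows the description of sociodemographic characteristics and could be read as applying to baseline tables. An unadjusted randomised comparison is valid, and with about 20,000 women chance imbalance should be small. The allocation text may describe the make-up of the sample rather than stratified randomisation. Leaving out balancing factors makes standard errors conservative, and only as far as the factors are prognostic.

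Much of this stands, and it rules out several stronger readings:

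- A reader might infer that no adjustment is planned, or that the entry answer, region and class are excluded. The text does not say so. Adjustment is present but directed at another question.
- A reader might infer that the effect is fixed as a within-arm change. No within-arm test is specified, and both the Abstract and the rest of the Statistical Analysis section describe group comparisons. The wording is ambiguous, no more.
- A reader might quote a gain equivalent to 33% to 96% more participants. That is 1/(1 − r²) − 1 at r = 0.5 and 0.7. The documents do not support choosing that range, and for a rare binary item r may well be lower.

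What does not fall away is the purpose that the article itself gives to the regression, the absence of any other named group test, and the conflict between the entry-exit wording and the between-group wording. These are stated in the published text, so they are not simply details left to an analysis plan.

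**Conclusion.** The point holds as one of efficiency and clarity. It does not show bias or inflated type I error. The article assigns regression to the influence of baseline characteristics instead of an adjusted treatment effect, and it leaves open whether the reduction in elective cesarean preference is measured against entry or against control.

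For items asked twice, adjustment for the entry answer would remove 4% of the variance at r = 0.2, 9% at 0.3, 25% at 0.5 and 49% at 0.7. This rests on an assumed r, on equal variances at entry and exit, and on the entry and exit items being close enough to pair; the article says only that the questionnaires are similar. Adding region and class alone may bring little. If the entry-exit wording were carried out as a change score, precision would be lower than with exit data alone for any r below 0.5.

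**What to change.** State one primary estimate: the between-arm contrast at exit, as a relative risk and a risk difference with 99% confidence intervals, from a standardised logistic regression or a Poisson regression with robust variance. Adjust for region, economic class and, where one exists, the same item's entry response. For birth-plan and engagement outcomes, adjust for region, class and related entry answers only.

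Keep the crude comparison as supportive. Keep the regression on baseline influence, if wanted, as a separate descriptive analysis. Reword the intention-to-treat sentence as a comparison of arms as randomised, and the Table 1 endpoint as the proportion at exit who intend to schedule an elective cesarean section, intervention versus control.

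The cost is a change of wording, made before outcomes are compared by arm. The covariates are already collected, and no extra participants or questions are needed.

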#### Qualitative Analysis

Audio narratives (entry and exit questionnaires and birth plan) will be automatically transcribed and analyzed in accordance with Bardin thematic analysis [54], using the Qualitative Solutions Research NVivo software (version 12.0, QSR International). A priori categories will include the following: feeling informed to make choices, feeling physically and emotionally secure, factors influencing satisfaction or dissatisfaction, desire to do something differently, and information needs. A posteriori categories are expected to emerge, as experience is considered an expansive learning opportunity [55].

### Data Monitoring and Auditing

Since this is an educational intervention with low risk among participants, no data monitoring committee has been contemplated. There will be no independent review of trial processes (data auditing) during its execution, as the whole trial will last less than a month and routine data quality management will be performed.

### Potential Risks to Participants

In this type of study, minimum risks are expected for the participants, such as the following: fatigue during the missions due to the long duration of the study or the lack of motivation with the topic of interest in the questionnaires; and discomfort or embarrassment if the participant is unaware of any term or situation presented during the study, despite efforts to adapt the language.

Another risk is the loss of data confidentiality, which will be minimized with protection measures by the researchers, as outlined during data collection and management. At the app level, users have preserved and guaranteed the rights to their data under the terms of the Brazilian General Data Protection Law.

## Results

The digital trial started recruiting participants in late October 2020, and data collection has been projected to be completed by December 2020.

The study will be conducted in accordance with Resolutions 466/2012 and 510/2016 of the National Health Council [52,56]. Information regarding personal interest will be obtained exclusively for the study, and privacy, confidentiality, and preservation of the participants’ identity will be ensured. Furthermore, the protection of data of all users of the digital platform, where the intervention will be applied, comply with the procedures outlined in accordance with the Brazilian General Data Protection Law.

Participation in the study must be voluntary and will be confirmed only after digital validation of the informed consent form. The study was approved by the institutional review board of Hospital Israelita Albert Einstein (project# 4194-20) and by the National Commission for Ethics in Research of the National Health Council of the Ministry of Health (CAAE: 32840920.7.0000.0071).

App users will individually provide consent to participate in the study. The risk to confidentiality will be minimized through protection measures by the researchers. All participants’ personal data and responses to participation will be kept private and confidential, thus guaranteeing anonymity, and at no time will participant identity be disclosed.

The data will be accessed only by the investigators. Since this is an educational intervention, it is of low risk, and no adverse effects are expected, and no compensation for study participation is contemplated.

## Discussion

There are presently no intentions to implement major protocol modifications; in case they occur, relevant parties will be solicited.

No restrictions are anticipated among investigators and sponsors to communicate trial results. We expect to disseminate the outcomes to the general public, health providers, and through scientific publications by means of a joint collaboration of the School of Public Health, University of São Paulo, with Sociedade Beneficente Israelita Brasileira Hospital Albert Einstein. The research teams from both institutions will author the resulting publications, with no intention to use professional manuscript writing services.

We will request authorization from the sponsor to grant public access to the complete protocol, anonymized participant-level data set, and the statistical code, 2 years after the completion of the study for both research and educational purposes, and to explore new hypotheses arising from the study.

If successful, this educative intervention (which can be used outside of the smartphone app) will be made publicly accessible after the dissemination of results, with proper credit and recognition.

## Appendix

Multimedia Appendix 1 Eligibility criteria filter questionnaire screenshot.

Multimedia Appendix 2 Invitation questionnaire screenshot.

Multimedia Appendix 3 Informed consent questionnaire screenshot.

Multimedia Appendix 4 Entry and exit questionnaire screenshot.

Multimedia Appendix 5 Intervention questionnaire screenshot.

Multimedia Appendix 6 Control questionnaire screenshot.

Multimedia Appendix 7 Birth plan questionnaire screenshot.

Multimedia Appendix 8 Childbirth styles screenshot.

Multimedia Appendix 9 Schedule of enrolment, interventions, and assessments.
